##### MRI visit (B1.1 and B2.1)

2.5.5.1.

In the psychophysiology laboratory, the participant completes the two practice tasks (see Section 2.4.5) in the presence of the researcher. If more practice is needed, a practice test is repeated. The intensity of electric shocks is determined by a calibration procedure (for details, see Supplementary Material S9). The participant then performs the fear acquisition task with psychophysiological assessment (pupil, skin conductance, heart rate). After a lunch break, the participant completes several online questionnaires, followed by a practice session in the dummy MRI laboratory and a second break. Subsequently, they provide a baseline saliva sample, which is followed by the oral intake of the study medication (indistinguishable capsule with 20 mg hydrocortisone or placebo). During the experimental set-up for the MRI session, the participant provides another saliva sample 30 minutes after medication administration. Heart rate and respiratory data are collected throughout the MRI session. The first part of the MRI session consists of a field map and task-based fMRI during fear extinction (45–55 minutes after medication administration) with psychophysiological assessment (pupil, skin conductance, heart rate). This is followed by a structural scan (T1-weighted during the first session; diffusion tensor imaging during the second session). During a short break, another saliva sample is provided (60–75 minutes after medication administration). The second part of the MRI session consists of resting-state fMRI with field mapping, and task-based fMRI during emotion processing with field mapping.

##### Next-day visit (B1.2 and B2.2)

2.5.5.2.

The participant completes online questionnaires and returns to the psychophysiology laboratory to complete the extinction recall task with psychophysiological assessment (pupil, skin conductance, heart rate). This visit is always scheduled the next day in the late afternoon, with an interval of at least 24 hours between the start of the fear extinction task and extinction recall task.

#### Follow-up survey

2.5.6.

An online survey is sent out only to participants from the PTSD group 9 months after the last visit of the observational study (i.e. study visit A2) to assess, if applicable, their response to treatments (i.e. treatment as usual which is unrelated to the current study). This online survey includes the PCL-5 to assess PTSD symptomatology, and questions about receiving psychotherapy and/or pharmacological treatment for PTSD and other psychiatric disorders. The control group was screened to be from a healthy population and as such is not expected to participate in any form of psychiatric treatment; hence, they do not participate in the follow-up survey.

#### Additional patient data

2.5.7.

Participants recruited from a collaborating mental healthcare institution provide consent that the study team may request specific types of information about them from their mental healthcare institution. This includes results from CAPS-5 assessments, which, according to harmonized clinical practice protocols, should be administered prior to trauma-related treatment.

#### Reimbursement

2.5.8.

Participants are offered a financial reimbursement for their time investment and effort, of €92 for the observational study, €130 for the pharmacological intervention study, and €10 for completion of the follow-up survey. When a participant is excluded following a screening visit or discontinues their participation, they are offered a reimbursement equivalent to their contributions. In addition, participants receive compensation for travelling expenses.

### Statistical analysis

2.6.

Mitigation plans to adapt statistical analyses if extension of the data collection period is no longer feasible and the planned sample size is not achieved are described in the Supplementary Material (S12).

#### Observational study

2.6.1.

##### Primary outcome measures

2.6.1.1.

HPA-axis dysregulation is investigated with two procedures by repeated sampling of saliva. These saliva samples will be analysed for cortisol levels using a competitive electrochemiluminescence immunoassay. For the DST, the main parameter of interest is suppression of the cortisol awakening response (CAR) based on the area under the curve (AUC) of normal CAR and dexamethasone-suppressed CAR, calculated as (1 − AUC_DEX_/AUC_CAR_) × 100%. For the SECPT, the main parameter of interest is the AUC with respect to increase (AUC_i_) in the cortisol stress response (Pruessner et al., 2003). Other variables and parameters from both procedures will also be investigated. ELA is assessed with the MACE questionnaire, which provides scores on 10 subscales of abuse and neglect that add up to a total scaled score and a multiple trauma score. It also provides information on the ages of exposure. Blood samples will be analysed for DNA methylation status, genotyping, and mRNA levels. Glucocorticoid signalling is primarily indicated by methylation of glucocorticoid-related genes, including *NR3C1* and *FKBP5*, but mRNA levels and genotype interactions will also be assessed. Treatment response is operationalized as the reduction of self-reported PTSD symptoms according to PCL-5 questionnaire assessments.

##### Statistical modelling

2.6.1.2.

Replicate findings of HPA-axis dysregulation in PTSD patients relative to a control group of individuals without PTSD or history of early-life trauma.

Statistical analyses of HPA-axis dysregulation in the PTSD group versus the control group will be tested using analyses of variance (ANOVAs), with group as the predictor of interest, and inclusion of age and gender as covariates. False discovery rate (FDR) correction will be applied over the number ANOVA tests with different HPA-axis dysregulation outcome variables. Furthermore, model extensions will explore additional covariates such as lifestyle factors (smoking, alcohol use, and drug use), concurrent psychiatric symptoms, and (female) menstrual cycle.
2.Investigate associations between history of ELA and HPA-axis dysregulation.

Associations between ELA and HPA-axis dysregulation will be investigated in the PTSD group with linear regression models, with the inclusion of age and gender as covariates. FDR correction will be applied over the number of regression models with different HPA-axis dysregulation outcome variables and/or different ELA predictor variables. Additional linear regression models will explore additional covariates such as other relevant task variables (e.g. SECPT stress ratings, duration of hand in water), lifestyle factors (smoking, alcohol use, and drug use), concurrent psychiatric symptoms, and (female) menstrual cycle.
3.Investigate whether epigenetic markers of glucocorticoid signalling (such as methylation status of glucocorticoid-related genes) mediate the association between history of ELA and HPA-axis dysregulation.

As a validation check of the proposed epigenetic mechanism, it will first be ascertained that for both genes *NR3C1* and *FKBP5* (and potentially other genes of interest), DNA methylation inversely correlates with mRNA levels in the blood. This will be tested with Pearson or Spearman correlation tests. Linear regression models will then investigate the associations between ELA and DNA methylation at *NR3C1* and *FKBP5* in the PTSD group, with the inclusion of age and gender as covariates. For *FKBP5*, we will take into account polymorphisms of SNP rs1360780 (minor risk allele T versus homozygous C-allele carriers) by specification of an ELA-by-genotype interaction effect, because of previously reported allele-specific gene–childhood effects (Klengel et al., 2013). FDR correction will be applied over the number of regression models with different DNA methylation outcome variables and/or different ELA predictor variables. The association between DNA methylation status and HPA-axis dysregulation will also be investigated with linear regression models, with the inclusion of age and gender as covariates. FDR correction will be applied over the number of regression models with different HPA-axis dysregulation outcome variables and/or different DNA methylation predictor variables. Additional linear regression models will explore additional covariates, such as other relevant task variables (e.g. SECPT stress ratings, duration), lifestyle factors (smoking, alcohol use, and drug use), concurrent psychiatric symptoms, and (female) menstrual cycle. If appropriate, regression models will be followed up by mediation models to directly test mediation of the association between ELA and HPA-axis dysregulation by methylation status of glucocorticoid-related genes.
4.Exploratively, investigate whether HPA-axis dysregulation and glucocorticoid signalling are associated with treatment response.

In the PTSD group, functional markers of HPA-axis dysregulation associated with treatment response will be examined with mixed-effects linear regression models. Since the PTSD group will have experienced heterogeneous courses of treatment, a specific analysis plan will be drafted after exploration of the frequency and variety of treatments within the sample.

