### Population

2.2.

This study aims to include *n *= 160 people with PTSD (part A), half of whom participate in the entire study (*n = *80 for part B). In addition, *n *= 30 control group participants are recruited (part A). All participants must be aged 18–64 years old. Exclusion criteria for both groups are listed in Table 1. More details on criteria assessed during the screening visit and amendments during the trial are listed in the Supplementary Material (S1 and S2). Power calculations are also described in the Supplementary Material (S3).

**Table 1. T0001:** Exclusion criteria.

Group	Exclusion criteria
PTSD	General exclusion criteria:
	- Current psychotic or manic episode
	- Benzodiazepine medication: Daily intake of benzodiazepines, or otherwise irregular intake of benzodiazepines (‘when needed’) but unable to withhold intake according to study procedures Exception: low evening doses (sleep medication)
	- For part B only: MRI contraindications
	Criteria assessed during screening session:
	- Does not receive a classification of current PTSD according to clinical interview assessment
Control	General exclusion criteria:
	- Current or past psychiatric disorder
	- Use of psychotropic medication
	- History of childhood maltreatment
	Criteria assessed during screening session:
	- Early-life adversity according to questionnaire assessment
	- (History of) psychiatric disorders according to clinical interview assessment
Both	General exclusion criteria:
	- General learning disability or intellectual disability
	- Body mass index > 35 kg/m^2^
	- Pregnancy or breastfeeding
	- Substance use: Unable or unwilling to withhold recreational drug use and limit alcohol use according to study procedures
	- Nicotine smoking: Unable or unwilling to discuss frequency and timing of smoking according to study procedures
	- Glucocorticoid medication/supplements: Current or recent regular use of systemic corticosteroids (< 1 month ago). For non-systemic corticosteroids, average use of more than once a week and/or no possibility to withhold according to study procedures
	- Hypersensitivity to glucocorticoids
	Criteria only if relevant to study outcomes or feasibility of study procedures:
	- Relevant neurological disorder
	- Severe physical disorder
	- Relevant endocrine disease and/or current or recent endocrine treatment

Note: MRI = magnetic resonance imaging; PTSD = post-traumatic stress disorder; BMI = body mass index.

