#### Control group

2.2.2.

The control group is screened for having no history of psychiatric disorders, no history of childhood trauma or maltreatment, and no current use of psychotropic medication (for details see Supplementary Material S1). Control participants will be selected based on age, gender, and education, with the aim of matching the distributions of these demographic variables to the (expected) distributions within the PTSD group.

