### Strengths and limitations

3.3.

The current study protocol describes an integrated and comprehensive study, which is conducted by a multidisciplinary team. The application of experimental tasks and procedures as part of assessments to a clinical group of PTSD patients allows mechanistic insights with a high potential for translation to clinical practice. As such, this study may pave the way for future clinical studies that investigate personalized PTSD treatment. The current study also has some limitations. For example, self-report questionnaires are used to assess symptomatology at follow-up. These are considered less reliable than structured clinical interviews such as CAPS-5, but assess a greater range of symptoms while placing less burden on participants (and may thus also show increased response rates). The current study only includes a CAPS-5 screening visit for PTSD participants recruited from the general population. PTSD participants who are recruited from local health mental institutes do not participate in this screening visit; here, we rely on harmonized clinical practice protocols for PTSD classification and treatment indication that include the administration of CAPS-5. Although PTSD classification is not verified by the study team prior to participation (owing to logistical challenges), participants provide consent so that we may receive this information from the local health mental institutes at a later stage. Of note, necessary amendments during the collection of study data resulted in additional limitations. Inclusion of PTSD group participants from the general population may lead to a selection bias of participants with chronic/complex PTSD who have particular interest in our stress system dysregulation hypotheses. It also increases the subgroup of participants that receives no PTSD treatment shortly after study participation and otherwise increases variability in treatment trajectories. This complicates the utility of treatment outcome follow-up measurements, but was necessary to increase inclusion rates.

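### The objective 1 PTSD-control comparison adjusts only for age and gender, leaving out education (a matching factor) and having no check for psychotropic medication, which is barred only in controls

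*Protocol article*

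**What the plan says.** Under Statistical modelling for the observational study (2.6.1.2), the objective 1 ANOVA is specified "with group as the predictor of interest, and inclusion of age and gender as covariates". Further variables enter only as exploration: "model extensions will explore additional covariates such as lifestyle factors (smoking, alcohol use, and drug use), concurrent psychiatric symptoms, and (female) menstrual cycle". Neither education nor prescribed psychotropic medication is named. The drug use that is named stands under lifestyle factors beside smoking and alcohol, so it reads as recreational use.

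Two other sections bear on this comparison.

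- Control group (2.2.2): "Control participants will be selected based on age, gender, and education". The aim is to match the distributions of these three variables to those expected in the PTSD group.
- Population (2.2), Table 1: one of the control exclusions is "Use of psychotropic medication". For the PTSD group the only psychotropic restriction is on benzodiazepines, with an exception for low evening doses taken for sleep.

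The objective 2 and 3 regressions carry the same two covariates. The ELA-HPA models "will be investigated in the PTSD group with linear regression models, with the inclusion of age and gender as covariates". The ELA-methylation models are run "in the PTSD group, with the inclusion of age and gender as covariates", with an added ELA-by-genotype term for *FKBP5*. The methylation-HPA associations "will also be investigated with linear regression models, with the inclusion of age and gender as covariates".

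**The concern.** Objective 1 is meant to replicate HPA-axis dysregulation in PTSD. Psychotropic use is 0% in controls by design and, benzodiazepines aside, unrestricted in patients. Any effect of such drugs on the cortisol measures therefore goes entirely into the group term. It could create a difference or hide one, because the document gives no direction.

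Education is the lesser part. Three variables are used to select controls, two of them enter the model, and the third does not. Matching is to an expected distribution and only at group level, so with 30 controls some imbalance may remain. Age and gender are protected against that by adjustment, and education is not.

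At stake is whether a positive result under objective 1 can be read as a feature of PTSD, or a null result as a failure to replicate.

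**Working it through.** The article gives no figure to reproduce: the power calculations are in Supplement S3, which is not shown. What follows is an illustration of scale.

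**Inputs from the document (2.2):** 160 PTSD and 30 control participants in part A; 0% of controls on psychotropic medication.

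**Assumed:** two-sided alpha 0.05, 80% power, outcome SD of 1, medicated share *p* of the PTSD group 25%, 50% or 75%, additive drug effect *b* of 0.2, 0.4 or 0.6 SD (absolute size).

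**Step 1. Precision of the planned contrast.**
SE = √(1/160 + 1/30) = √0.03958 = 0.199 SD.
Detectable difference = (1.96 + 0.84) × 0.199 = 0.56 SD.

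**Step 2. Bias from ignoring medication.** With no medicated controls, bias = *p* × *b*. If PTSD itself had no effect, the rejection probability is 1 − Φ(1.96 − *m*) + Φ(−1.96 − *m*), with *m* = *pb*/0.199.

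| *p* | *b* = 0.2 | *b* = 0.4 | *b* = 0.6 |
|---|---|---|---|
| 25% | 0.05 SD; 5.7% | 0.10 SD; 7.9% | 0.15 SD; 11.7% |
| 50% | 0.10 SD; 7.9% | 0.20 SD; 17.1% | 0.30 SD; 32.6% |
| 75% | 0.15 SD; 11.7% | 0.30 SD; 32.6% | 0.45 SD; 61.9% |

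Each cell gives the bias, then the true type I error against a nominal 5%. FDR correction over several HPA outcomes controls multiplicity and does not remove a bias.

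**Step 3. Precision of a contrast restricted to unmedicated PTSD participants.** SE = √(1/[160(1 − *p*)] + 1/30).

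- *p* = 25%: √(1/120 + 1/30) = 0.204, detectable difference 0.57 SD.
- *p* = 50%: √(1/80 + 1/30) = 0.214, detectable difference 0.60 SD.
- *p* = 75%: √(1/40 + 1/30) = 0.242, detectable difference 0.68 SD.

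The loss is modest because the 30 controls dominate the variance. Without other covariates, putting a medication indicator into the ANOVA yields this same comparison, since no control is medicated.

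**Education.** The bias is the residual imbalance multiplied by the slope of the outcome on education. The document gives neither, so no number is offered.

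**The case against.** The exploratory list is introduced by examples and is open. Section 2.2.1 mentions hormonal contraceptive use as a possible confounder, and that is not in the list either, so absence from it does not prove that medication or education will be ignored. Matching already deals with education if it succeeds, and nothing in the article links education to cortisol. Medication use may also follow from PTSD severity, so an unmedicated subset may be milder and answers a narrower question than whether PTSD patients as a group differ from controls.

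Much of this stands. It is why the all-patient contrast should remain the main analysis and the medication check should be a companion to it. It does not remove the point. An open list commits to nothing, and the medication asymmetry comes from the article's own eligibility criteria. Education is the only one of three matching factors left out of the model.

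A reader might go further and infer that objectives 2 and 3 are also biased, because patients have been recruited from the general population as well as from clinics since January 2023. The Strengths and limitations section (3.3) concedes: "Inclusion of PTSD group participants from the general population may lead to a selection bias of participants with chronic/complex PTSD". If route correlates 0.1-0.4 with ELA and 0.1-0.3 with the HPA outcome, the induced correlation is the product, 0.01 (0.1 × 0.1) to 0.12 (0.4 × 0.3), with rejection rates of 5.2% to 33% at n = 160. But that treats the whole route-HPA link as unrelated to ELA, and the document does not support this. The Introduction traces complex PTSD back to ELA and gives ELA a possible role in HPA dysregulation. A difference between routes may then be the very association objective 2 seeks, and adjusting for route could remove real ELA variance. Nor does the article link medication to ELA. Neither variable can be called a required covariate in those models.

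**Conclusion.** The point holds for objective 1. As written, the PTSD-control ANOVA cannot tell a PTSD effect from a psychotropic medication effect, and it leaves one of three matching factors unadjusted. Medication is the more important of the two; education is a minor consistency point.

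The size is unknown. The range of 0.05-0.45 SD rests wholly on the assumed medicated share and drug effect, an SD of 1 and additivity. At the upper end it approaches the 0.56 SD detectable difference; at the lower end it is negligible. The document does not show that a bias has occurred or in which direction.

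For objectives 2 and 3, no defect in the base models is established. Showing the results with psychotropic use or recruitment route added is an option and no more.

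**What to change.** 1. Add education to the objective 1 ANOVA beside age and gender.
2. Keep the contrast of all PTSD participants with controls as the main analysis of objective 1.
3. Prespecify a sensitivity analysis comparing PTSD participants who use no psychotropic medication with controls, and state that this subset is smaller and may be less severely ill. Agreement with the main result would be reassuring; disagreement would not by itself show that medication is the cause.
4. Optionally, for objectives 2 and 3, show models with psychotropic use and recruitment route beside the base models, without replacing them.

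The cost is one degree of freedom for education if it enters as a single term (more if it is categorical), and a less precise sensitivity contrast: SE about 0.21 versus 0.20 SD if half are medicated. This assumes that medication use is recorded beyond what the benzodiazepine criterion needs. At March 2024 the observational study had completed visits for 55 of the planned 160 PTSD participants, so at that stage the change could still be written in before analysis.

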In PTSD, enhanced HPA-axis feedback regulation can lead to exaggerated suppression of cortisol, which results in lower circulating cortisol levels (Goenjian et al., 1996; Grossman et al., 2003; Pitman et al., 2012; Stein et al., 1997; Yehuda, 2009; Yehuda et al., 1993, 1995, 2002, 2004). Although most meta-analyses support this notion of HPA-axis dysregulation (Meewisse et al., 2007; Morris et al., 2012; Pan et al., 2018), another meta-analysis (Klaassens et al., 2012) and multiple studies that failed to replicate these findings suggest that low cortisol may only be observed under certain conditions, perhaps only within subgroups of individuals with PTSD (Meewisse et al., 2007; Pitman et al., 2012; Zoladz & Diamond, 2013). DNA methylation can suppress gene transcription and, as such, contribute to individual differences in glucocorticoid signalling (Turecki & Meaney, 2016; Zhang et al., 2013). Previous research indicated that decreased methylation of the glucocorticoid receptor (GR) gene *NR3C1* is associated with ELA (Oberlander et al., 2008; Parent et al., 2018; Weaver et al., 2007). Moreover, allele-specific DNA demethylation of *FKBP5* (a co-chaperone that regulates GR activity) mediates gene-by-ELA interactions and induces long-term HPA-axis dysregulation (Klengel et al., 2013; Koenig et al., 2018; Mehta et al., 2011). HPA-axis dysregulation and methylation status of *NR3C1* and *FKBP5* are also associated with increased lifetime risk for PTSD development if exposed to traumatic events (Labonté et al., 2014; van Zuiden et al., 2011; Vukojevic et al., 2014; Yehuda et al., 2015b). Beyond these observational findings, experimental research with rodents has provided causal support that ELA can lead to HPA-axis dysregulation. ELA was shown to cause lower glucocorticoid levels, which was accompanied by an upregulation of GRs within the hippocampus and medial prefrontal cortex and decreased later-life social behaviour, of which the latter was reinstated with glucocorticoid administration (Perry et al., 2019). Gene expression patterns thus tune the sensitivity of the stress response and negative feedback inhibition via epigenetic mechanisms.

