Collectively, the aforementioned findings suggest a mechanistic model in which PTSD patients with dysfunctions in glucocorticoid signalling – potentially emerging from epigenetic programming by ELA – insufficiently benefit from PTSD treatments. This group of non-responding and relapsing individuals could potentially benefit from exogenous glucocorticoid administration during extinction learning (De Quervain et al., 2019). The current study integrates an observational study with a pharmacological intervention and functional resonance imaging (fMRI) study to provide a translational effort towards improved and personalized PTSD treatment. In our observational study, we investigate interaction effects of ELA and epigenetic programming of glucocorticoid signalling on HPA-axis regulation and their association with treatment outcome in a group of individuals with PTSD. The pharmacological intervention and fMRI study investigates glucocorticoid-induced enhancement of extinction learning in PTSD patients in a placebo-controlled clinical trial with a crossover design. By leveraging an experimental fear conditioning and extinction task within a virtual environment that uses houses as spatial contexts for the experiences, we will be able to investigate the effect of exogenous glucocorticoids on the context dependency of fear and extinction memories. Overall, we aim to provide proof of concept that HPA-axis dysregulation in individuals with PTSD is related to ELA and associated epigenetic markers of glucocorticoid signalling; that these individuals with PTSD show impairments in extinction learning and altered neural responses; and that this subgroup would particularly benefit from glucocorticoid augmentation of extinction learning through a mechanism of enhancing the strength and generalization of extinction memories.

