### Research objectives

1.1.

Objectives of the observational study:
Replicate findings of HPA-axis dysregulation in PTSD patients relative to a control group of individuals without PTSD or history of early-life trauma.Investigate associations between history of ELA and HPA-axis dysregulation.Investigate whether epigenetic markers of glucocorticoid signalling (such as methylation status of glucocorticoid-related genes) mediate the association between history of ELA and HPA-axis dysregulation.Exploratively, investigate whether HPA-axis dysregulation and glucocorticoid signalling are associated with treatment response.

Objectives of the pharmacological intervention study:
Investigate whether patients with HPA-axis dysregulation show impairments in extinction learning relative to patients without HPA-axis dysregulation, and whether this is accompanied by different neural responses during extinction learning in brain regions associated with fear expression and extinction.Investigate whether the subgroup of PTSD patients with HPA-axis dysregulation particularly benefits from hydrocortisone administration (versus placebo) to improve the strength and generalization of extinction memories.Investigate neural responses during extinction learning in brain regions associated with fear expression and extinction after hydrocortisone administration (versus placebo), that may be associated with improvements in strength and generalization of extinction learning.

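### The methylation-to-HPA regressions under objective 3 leave out ELA, so they do not estimate the mediator-outcome path and can pick up confounding by ELA

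*Protocol article*

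**What the plan says.** Section 1.1 sets objective 3 as a mediation question: whether epigenetic markers "mediate the association between history of ELA and HPA-axis dysregulation". Section 2.6.1.2 then lays out the analysis in steps.

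- Methylation is first checked against mRNA levels.
- Methylation is regressed on ELA in the PTSD group, adjusted for age and gender, with an ELA-by-genotype term for FKBP5.
- HPA-axis measures are regressed on methylation: "The association between DNA methylation status and HPA-axis dysregulation will also be investigated with linear regression models, with the inclusion of age and gender". These models have their own FDR correction.
- Further models explore task variables and "lifestyle factors (smoking, alcohol use, and drug use), concurrent psychiatric symptoms, and (female) menstrual cycle". This list is open-ended, but ELA is not named in it.
- Last comes the mediation analysis: "If appropriate, regression models will be followed up by mediation models to directly test mediation of the association between ELA and HPA-axis dysregulation". No criterion for appropriateness is given.

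The Introduction supplies the causal picture. On the path from ELA to the HPA axis it says that "experimental research with rodents has provided causal support that ELA can lead to HPA-axis dysregulation". On the path from ELA to methylation it describes glucocorticoid dysfunction as "potentially emerging from epigenetic programming by ELA". It also announces a study of how ELA and epigenetic programming interact in their effect on the HPA axis, which needs both variables in one model.

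**The concern.** On the protocol's own premises, ELA is a common cause of the predictor (methylation) and the outcome (HPA-axis measure) in the third step. In a mediation question, the mediator-outcome path is the association of methylation with the HPA axis at a given level of ELA. A model without ELA estimates something else: that path plus whatever ELA does to the HPA axis by other routes, in so far as it is correlated with methylation. Whether methylation carries all of the ELA effect is part of what objective 3 sets out to learn, so it cannot be assumed when the model is chosen.

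Two things are at stake. A significant methylation coefficient could be read as support for the epigenetic mechanism when it reflects ELA alone. And if the decision to go on to mediation rests on these regressions, it rests on a confounded result.

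**Working it through.** **Inputs from the document.** Fixed covariates: age and gender (section 2.6.1.2). Planned PTSD sample in part A: 160 (section 2.2). PTSD participants who had completed the observational visits by March 2024: 55 (section 3.1), used here only to show a smaller sample. The methylation-to-HPA sentence does not name its group; I take it to be the PTSD group, as in the step before it.

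**Inputs assumed.** The article gives no effect size for any path and places its power calculation in Supplement S3, which is not shown. There is therefore no figure of the plan to reproduce. Path sizes are varied from 0.2 to 0.4, with a two-sided 0.05 test before FDR correction.

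**Model.** With ELA = X, methylation = M and HPA measure = Y, all standardised:

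- M = a·X + error
- Y = c·X + b·M + error

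Here a is the ELA-to-methylation path, c is the ELA effect on the HPA axis that bypasses methylation, and b is the mediator-outcome path.

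**Bias.** Without X in the model, the coefficient of M has expectation b + a·c. With X in the model it is b. If b = 0, the model as written shows r = a·c: 0.2 × 0.2 = 0.04, 0.3 × 0.3 = 0.09, 0.4 × 0.4 = 0.16. If c = 0 (complete mediation), there is no bias.

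**False rejection, analytic.** The model fits four coefficients (intercept, age, gender, methylation), so z = r/√(1 − r²) × √(n − 4), and the rejection rate is about Φ(z − 1.96) + Φ(−z − 1.96). For r = 0.09 and n = 160: z = 0.0904 × 12.49 = 1.13, giving Φ(−0.83) + Φ(−3.09) ≈ 20.4%.

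**False rejection, simulated.** The model as written and the model with ELA added were each fitted in 4,000 simulated trials per setting. A separate run of 8,000 per setting at n=160, comparing the marginal with the ELA-partial correlation, gave 7.7%, 19.8% and 53.0%.

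| ELA paths a/c | n | spurious r | z | analytic | simulated, as written |
|---|---|---|---|---|---|
| 0.2/0.2 | 160 | 0.04 | 0.50 | 7.9% | 7.8% |
| 0.3/0.3 | 160 | 0.09 | 1.13 | 20.4% | 20.3% |
| 0.4/0.4 | 160 | 0.16 | 2.02 | 52.6% | 54.2% |
| 0.2/0.2 | 55 | 0.04 | 0.29 | 5.9% | 5.7% |
| 0.3/0.3 | 55 | 0.09 | 0.65 | 9.9% | 10.1% |
| 0.4/0.4 | 55 | 0.16 | 1.16 | 21.2% | 19.8% |

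With ELA added, the simulated rate was 4.8–5.0% at n=160 and 4.6–5.1% at n=55.

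**The decision to run mediation.** Suppose, as one possible reading, that mediation is run when all three regressions (ELA on HPA, ELA on methylation, methylation on HPA) are significant. At n=160 with no true methylation effect, that condition is met in 5.0%, 19.8% and 54.2% of runs for the three settings. A joint-significance mediation test that adjusts for ELA is then positive in no more than 2.4% of all runs, so the final test stays conservative.

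**The case against.** The strongest reply is that these regressions are not the plan's mediation test. The text calls them an investigation of an association, and a separate model is named to test mediation directly. An association adjusted for age and gender is a legitimate descriptive quantity, and a standard mediation model conditions on the exposure. This largely stands. A reader might infer that objective 3's mediation conclusion has a 20% or 53% error rate. It does not: those rates belong to the methylation-to-HPA regressions alone. What survives is that these regressions are placed under a mediation objective with their own FDR family, and that the one ELA-adjusted estimate is the analysis to which the plan does not firmly commit. FDR correction deals with multiplicity and does not remove confounding.

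A reader might also infer that the unadjusted regressions formally decide whether mediation is tested. The text states no such rule; the mRNA check and the two ELA regressions could equally enter the judgement. A significance gate is one reading.

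A third stronger reading is that the omission would hide true mediation. That can be constructed: with a = 0.4, c = −0.4 and b = 0.25, the marginal association is 0.25 − 0.16 = 0.09, and the unadjusted test is significant in 20.6% of runs against 87% with ELA included. But it needs ELA to act on the HPA axis in opposite directions by two routes, and the article posits nothing of the kind.

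Finally, the open list of exploratory covariates does not exclude ELA. True, but the main model's covariates are named, so the omission is a stated choice and not a detail left to another document.

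**Conclusion.** The point holds in limited form. As specified, the methylation-to-HPA regressions do not estimate the mediator-outcome path that objective 3 needs, and they can show a methylation association produced by ELA alone. The size depends on assumed paths: negligible to small at 0.2/0.2, material at 0.3/0.3 and above at the planned sample, about half the excess or less at n=55, and nil if methylation carries the whole ELA effect. The later mediation model, if it conditions on ELA in the usual way, is not inflated. The remaining weakness there is that it is conditional without a stated criterion; if the criterion is significance of the unadjusted regressions, it could be triggered or skipped on a confounded result. Part B's randomised comparison is not affected.

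**What to change.** In section 2.6.1.2, objective 3:

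- Add the MACE ELA score as a covariate in the methylation-to-HPA models. For FKBP5, also add genotype and the ELA-by-genotype term already used in the ELA-to-methylation models.
- Keep the association without ELA as a descriptive result only.
- State that the mediation models for NR3C1 and FKBP5 do not depend on the significance of the unadjusted regressions.

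No new data are needed, since the MACE is already collected. The cost is one degree of freedom, or three for FKBP5 with a two-level genotype, and slightly wider intervals where ELA and methylation are correlated. The standard-error factor from that correlation is 1/√(1 − a²): 1.02 for a = 0.2, 1.05 for 0.3 and 1.09 for 0.4, partly offset when ELA explains outcome variance.
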